## Abstract

**Background:**

Pancreatic cancer, predominantly characterized by ductal adenocarcinoma (PDAC) accounts for 90% of cases and is the fourth leading cause of cancer-related deaths globally. Its incidence is notably increasing. This poor prognosis is primarily due to late-stage diagnosis (approximately 70% to 80% of patients are diagnosed at an advanced stage), aggressive tumor biology, and low sensitivity to chemotherapy. Consequently, it is crucial to identify and develop a simple, feasible and reproducible blood-based signature (i.e., combination of biomarkers) for early detection of PDAC.

**Methods:**

The PANLIPSY study is a multi-center, non-interventional prospective clinical trial designed to achieve early detection of PDAC with high specificity and sensitivity, using a combinatorial approach in blood samples. These samples are collected from patients with resectable, borderline or locally advanced, and metastatic stage PDAC within the framework of the French Biological and Clinical Database for PDAC cohort (BACAP 2). All partners of the BACAP consortium are eligible to participate. The study will include 215 PDAC patients, plus 25 patients with benign pancreatic conditions from the PAncreatic Disease Cohort of TOuLouse (PACTOL) cohort, and 115 healthy controls, totaling 355 individuals. Circulating biomarkers will be collected in a total volume of 50 mL of blood, divided into one CellSave tube (10 mL), two CELL-FREE DNA BCT® preservative tubes (18 mL), and five EDTA tubes (22 mL in total). Samples preparation will adhere to the guidelines of the *European Liquid Biopsy Society* (ELBS). A unique feature of the study is the AI-based comparison of these complementary *liquid biopsy* biomarkers.

Main end-points: *i)* to define a liquid biopsy signature that includes the most relevant circulating biomarkers, *ii)* to validate the multi-marker panel in an independent cohort of healthy controls and patients, with resectable PDAC, and *iii)* to establish a unique liquid biopsy biobank for PDAC study.

**Discussion:**

The PANLIPSY study is a unique prospective non-interventional clinical trial that brings together liquid biopsy experts. The aim is to develop a biological signature for the early detection of PDAC based on AI-assisted detection of circulating biomarkers in blood samples (CTCs, ctDNA, EVs, circulating immune system, circulating cell-free nucleosomes, proteins, and microbiota).

**Trial registration:**

ClinicalTrials.gov Identifier: NCT06128343 / NCT05824403. Registration dates: June 8,2023 and April 21, 2023.

## Background

Pancreatic cancer (PC) is currently the fourth leading cause of cancer-related deaths worldwide. Over the past two decades, its prevalence has steadily risen, particularly in Europe, with 150,000 new cases reported in 2018 and 95,000 deaths per year (Global Cancer Observatory (iarc.fr)). Moreover, PC has the worst prognosis of any cancer type in Europe, with a median survival time of 4.6 months. Consequently, it is projected that by 2030, PC will become the second leading cause of cancer-related deaths in Europe and globally. In France, the incidence of PC increased from 7,500 cases per year in 2009 to over 14,000 per year in 2018, with 11,456 deaths reported in 2018 (5-year overall survival rate: 11%). This poor prognosis can be attributed to the late-stage diagnosis of PC in approximately 70%-80% of patients (~ 50% of patients are diagnosed with stage IV PC), its aggressive biology, and the partial response to currently available chemotherapies. Furthermore, there is no effective screening program due to the absence of a biological test for early PC detection. Therefore, the most significant challenge in managing PC is early detection, especially in patients where PC has not developed yet, such as patients at risk (PAR) and patients with pre-neoplastic cystic lesion of the pancreas (PPNL), such as intraductal papillary mucinous neoplasms. Despite promising studies on early PC biomarkers, particularly in risk groups (PAR, PPNL), no biomarker suitable for clinical diagnosis has been identified [1]. Carbohydrate antigen 19–9 (CA19-9) is the most commonly used and evaluated blood-based PC biomarker; however, its specificity is limited as elevated CA19-9 levels are also associated with other clinical conditions [2]. In this context, it is critical to identify and develop a simple, feasible, and reproducible biomarker.

Currently, pancreatic ductal adenocarcinoma (PDAC; the most common histological form of PC) is diagnosed using tissue biopsies (from the primary tumor or from secondary lesions) [3]. Tissue biopsies are typically performed with endoscopic (for resectable, borderline, or locally advanced primary tumor lesions), or radiological guidance (for metastatic lesions or when endoscopy is contra-indicated). Endoscopy-guided biopsies are often technically challenging to perform, making them operator-dependent and occasionally ineffective. In the worst-case scenario, a single patient may undergo repeated invasive procedures without receiving a definitive diagnosis. Complications of endoscopy-guided biopsy include bleeding, duodenal perforation, and more commonly acute pancreatitis. Severe acute pancreatitis may delay the tumor surgical removal or postpone a new tissue biopsy, if the previous biopsy was not contributive. In this context, it is crucial to develop an alternative method to tissue biopsies for PC diagnosis. Lastly, despite advances in radiological work-up (thoraco-abdomino-pelvic CT and liver MRI), patients with upfront resectable PC frequently experience early post-operative progression, most likely due to the failure to detect infra-clinic metastatic disease. Therefore, to improve the prognosis of patients with PC, new biomarkers are required for earlier, pre-symptomatic diagnosis.

Blood-based biomarkers, such as circulating tumor cells (CTCs), circulating cell-free tumor DNA (ctDNA), extracellular vesicles (EVs), circulating cell-free nucleosomes (cfnucleosomes), circulating cell-free proteins, circulating immune cells (CIC), and circulating microbiota, may serve as potential indicators of tumor burden in patients with cancer. These minimally invasive "*liquid biopsies*” (*LB*) have garnered significant attention due to their clear clinical implications for personalized medicine, such as the identification and stratification of patients with cancer. *LB* were introduced as a new diagnostic concept in 2010 [4] and offer several clinical applications [5]. *LB* methods based on ctDNA methylation patterns for the early diagnosis of PC have shown promising results [6]; also, the detection of *KRAS*-mutated ctDNA was correlated to post-operative recurrence [7]. However, these *LB* approaches based on a single analyte might have a low positive predictive value and might not be sufficient for screening purposes [8, 9]. We believe that early cancer detection by *LB* needs to rely on a combination of appropriate circulating biomarkers to obtain a precise cancer profile in real-time [10]. *LB* use for the early detection of PDAC, which represents 90% of histologically proven PC, is of high public interest, but it faces serious challenges concerning the specificity and sensitivity of the current *LB*-based assays. Therefore, in this study we propose a systematic approach with the aim of assessing different, recently developed complementary *LB* biomarkers (CTCs, ctDNA, EVs, cfnucleosomes, proteins, CIC, and circulating microbiota) as a novel noninvasive method for the early detection of resectable PDAC. The main hypothesis of the PANLIPSY study is that the *LB* signature (combination of circulating biomarkers), identified using AI-based algorithms, may allow the detection of early-stage PDAC in blood samples from patients with pancreatic cancer and benign pancreatic lesions (prospective clinical trials BACAP 2 and PACTOL). This could improve the detection of PDAC at an early stage to enhance patients’ oncological outcomes.

## Methods and design

### Aims of PANLIPSY

The main objective of this non-interventional prospective clinical trial is to define a *liquid biopsy (LB)* signature that includes the most relevant analytes currently available: CTCs, ctDNA, circulating nucleosomes, circulating proteins, EVs, CICs, and circulating microbiota in blood samples from patients with histologically confirmed PDAC (all stages) compared to healthy controls (HCs) and patients with benign pancreatic diseases. This signature will combine the results of all *LB* analytes into a multi-marker panel, designed through computational combinatorial analysis with AI-based algorithmic approaches. In the second part of the study, this multi-marker panel will be validated in an independent cohort of HCs and patients with resectable PDAC. The project will also establish a unique liquid biopsy bio-bank for the PDAC study.

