### Study population

A total of 215 patients with PDAC, 25 patients with benign pancreatic conditions (BPC) and 115 age- and sex-matched HCs will be included during the study period.

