#### Sample size justification

DISCOVERY PHASE (85 patients with resectable PDAC and 85 HCs):

With a total sample size of 170 (*n* = 85 patients with resectable PDAC and *n* = 85 HCs), a two-sided 95% confidence level with an AUC = 0.85, produces a confidence interval width of 0.118 (distance from AUC to the limit = 0.059; nQuery software / Confidence interval for AUC).

VALIDATION PHASE (30 patients with resectable PDAC and 30 HCs):

The sample size is based on the recruitment potential from the BACAP cohort for a 12-month period of inclusion and corresponds to ~ 30% of the total sample.

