### Discovery phase

During the first 3.5 years, patients with resectable (*n* = 85), borderline or locally advanced stage (*n* = 50), metastatic PDAC (*n* = 50), and BPC (*n* = 25) will be included. Additionally, 85 age- and sex-matched HCs will be recruited at the end of this period (in-kind contribution of INOSPECIMENS from the Groupe INOVIE). All circulating biomarkers listed above will be detected in patients’ blood samples. The exploratory design is essential to precisely determine the best *LB* signature based on the cancer stage. Patients with BPC and HCs (control groups) will also be included to eliminate potential confounding markers, background noise, and misleading biological signatures. This discovery approach will also provide different *LB* signatures correlated with PDAC aggressiveness.

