### Statistical analysis

In this project, the first type of machine learning model we will train is random forests. These will be used to predict whether a patient will develop pancreatic cancer based on all measured markers and associated health data. The dataset collected in this project will be divided into three different subsets: a training set (60% of the samples), a test set (20% of the samples), and a validation set (20% of the samples). A stratified sampling approach will be used to ensure that each class is accurately represented in each set, especially if an imbalance between classes is present in the original dataset. The training and test subsets will be used to train the machine learning algorithms, while the validation subset will be used to ensure that the model is generalizable (i.e., it can accurately classify future samples that may be collected). We will use the out-of-bag error method (a bootstrapping procedure that trains the models on multiple subsets of the predictor variables) to quantify the relative contribution of each variable to the model's performance. In addition, the performance of each model will be quantified by calculating its accuracy, precision, and area under the curve (AUC). In the performance of the random forest models is not satisfactory, the same approach will be used, but this time using XGboost and artificial neural network models instead. This approach allows the complexity of the model to be gradually increased, with the aim of forming a parsimonious model with a good ability to distinguish between healthy and cancer patients. The performance of all models trained during this project will be compared to a multiple logistic regression model as a baseline model.

We will also explore the results of machine learning models in the inferential framework. Using generalized linear models, we will compare the mean of each marker retained by the best machine learning models, while controlling for confounding variables (e.g., age…). This approach will quantify the differences in markers between healthy and cancer patients and identify markers that may not be statistically significantly different between the two groups but still contribute to good machine learning performance (those variables are called "weak predictors").

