#### Endpoints

Measurements of CTCs, ctDNA, cfnucleosomes, circulating proteins, EVs, CIC, and circulating microbiota as defined above.Area Under the Curve (AUC) of the ROC curve of the multi-marker *LB* signature. Optimal threshold of the multi-marker *LB* signature that maximizes the Youden index.Dichotomized test at the optimal threshold: positive test (patients with resectable PDAC) if the *LB* signature is greater than or equal to the optimal threshold/negative test (HC) if the *LB* signature is lower than the optimal threshold.*Sensitivity*: the percentage of patients with resectable PDAC (gold standard = cytologically and/or histologically proven PDAC) with a positive LB signature test.*Specificity*: the percentage of HC with a negative LB signature test.

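### The signature and the models are defined on PDAC of all stages, and this is not reconciled with the resectable-versus-healthy contrast that the study is sized, measured and validated on

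*Protocol article*

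**What the plan says.** **All-stage side.** Under Aims of PANLIPSY, the signature is to be defined "in blood samples from patients with histologically confirmed PDAC (all stages) compared to healthy controls (HCs) and patients with benign pancreatic diseases". Under Statistical analysis, the modelling works towards "forming a parsimonious model with a good ability to distinguish between healthy and cancer patients", using "a training set (60% of the samples), a test set (20% of the samples), and a validation set (20% of the samples". Sampling is stratified by class, and class is not defined by stage. Each model is scored by accuracy, precision and AUC. If the random forest falls short, the same approach is repeated with XGBoost and neural networks. Neither the scoring nor that decision names a stage. The Highlights section likewise says that all stages are included in order to define the signature for very early disease.

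**Resectable side.** The Background gives early detection of resectable PDAC as the purpose. The sample size section sets out "DISCOVERY PHASE (85 patients with resectable PDAC and 85 HCs" as the discovery comparison. The Endpoints section defines sensitivity as "the percentage of patients with resectable PDAC (gold standard = cytologically and/or histologically proven PDAC) with a positive LB signature test" and specificity on healthy controls. Validation is 30 resectable patients against 30 healthy controls.

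**Mix of stages.** Discovery enrols "patients with resectable (*n* = 85), borderline or locally advanced stage (*n* = 50), metastatic PDAC (*n* = 50". The same section says that the design serves to find the best signature according to stage, but the Statistical analysis section attaches no fit, metric or decision to that statement.

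**The concern.** The article gives two different contrasts for one signature and does not say which of them governs fitting and selection. If the Statistical analysis section is followed as written, markers are ranked, and models kept or replaced, on a cancer class of which more than half is not the target. The Background describes the analytes as possible indicators of tumour burden, so it is plausible that some of them separate advanced disease from controls better than they separate resectable disease.

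The choice of panel is at stake, as well as the figure reported for it. A protein library of 3000 assays offers many candidates, and markers that mainly respond to advanced disease could displace weaker ones that respond to resectable disease. Measuring sensitivity correctly afterwards would expose a poor panel but would not produce a better one.

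**Working it through.** **Inputs.** 85 resectable, 50 borderline or locally advanced and 50 metastatic patients, and 85 healthy controls (Discovery phase); 215 PDAC in all (Study population); AUC 0.85 with a 95% interval half-width of 0.059 (Sample size justification). The advanced-stage AUCs below are assumptions; the article gives none.

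**1. Which contrast the plan's own precision figure belongs to.** Hanley–McNeil variance, with A the AUC, n₁ cases and n₂ controls:

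Var = [A(1−A) + (n₁−1)(Q₁−A²) + (n₂−1)(Q₂−A²)] / (n₁n₂), where Q₁ = A/(2−A) and Q₂ = 2A²/(1+A).

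For A = 0.85: Q₁ = 0.7391, Q₂ = 0.7811, A² = 0.7225.

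- 85 v 85: Var = (0.1275 + 84×0.0166 + 84×0.0586)/7225; SE = 0.0299; half-width = 1.96 × 0.0299 = 0.0585. This rounds to the stated 0.059.
- 185 v 85 (all stages): SE = 0.0227; half-width = 0.0445. This is not the stated figure.

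The sizing therefore concerns resectable disease only, whereas the objective and the modelling text concern all stages.

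**2. Share of non-target cancers.** Discovery: (50+50)/(85+50+50) = 100/185 = 54.1%. If the dataset to be split is read as both phases together: 100/215 = 46.5%.

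**3. What a pooled AUC can hide.** For one score against the same controls, the pooled AUC is exactly the case-weighted mean of the stage AUCs:

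AUC(pooled) = (85/185) × AUC(resectable) + (100/185) × AUC(advanced).

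Hence AUC(resectable) = [0.85 − 0.5405 × AUC(advanced)] / 0.4595. The right-hand column repeats this for all 215 PDAC, with weights 0.4651 and 0.5349.

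| Assumed advanced-stage AUC | Resectable AUC, 185 pooled | Resectable AUC, 215 pooled |
|---|---|---|
| 0.85 | 0.85 | 0.85 |
| 0.90 | 0.79 | 0.81 |
| 0.95 | 0.73 | 0.76 |
| 0.97 | 0.71 | 0.75 |

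The first row matters: if stage makes no difference to the score, nothing is hidden.

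**4. Effect on marker choice (illustration, all settings assumed).** 300 markers were simulated for 85 resectable, 100 advanced and 85 healthy subjects. Ten markers had AUC 0.65 at every stage, ten had 0.55 in resectable and 0.85 in advanced disease, and the rest were noise. The ten markers with the highest AUC were kept and summed, and the score was evaluated on new subjects. Over 100 repeats, selection on the pooled class gave a mean resectable AUC of 0.70; selection on resectable cases gave 0.84. The pooled AUC was 0.86 both ways, so in this setting it could not tell the two panels apart. The marker mix was chosen to show the mechanism and says nothing about the true markers.

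**The case against.** The strongest reply is that the article already aims its decisive measures at resectable disease. This largely stands, and it rules out three stronger readings that a reader might infer.

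- *That the signature is accepted on an all-stage class.* Not supported. Sensitivity, specificity and the validation cohort are all resectable PDAC versus healthy controls.
- *That the cut-off is driven by late-stage disease.* Not shown. The Youden threshold sits in the same endpoint list as the dichotomised test, which is defined on resectable PDAC and healthy controls. The natural reading is that the threshold is set there, although the AUC and threshold lines do not name the class.
- *That a shortfall would first appear in validation.* Not supported. The discovery AUC is planned on 85 resectable v 85 healthy, so weak resectable performance could be seen before validation.

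Three further points are fair. The 0.85 is a planning value for resectable disease and not an acceptance bar; the article puts no number on adequate performance. Stage-based signatures are announced under Discovery phase, and an article may leave stage-specific fits to a fuller document. Training on 185 cancers and evaluating on the target stage is also a defensible choice when candidate markers are so many.

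What remains is a conflict in the text itself, not an omitted detail: the objective and the modelling section state a contrast that differs from the one in the sizing and endpoint sections. The resectable-only endpoint definitions do not govern marker selection or the step to more complex models.

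**Conclusion.** The point holds as an unreconciled contradiction with a practical risk. The signature is defined, and the models are judged, on PDAC of all stages versus non-cancer, while the target, discovery precision, sensitivity, specificity and validation are on resectable PDAC versus healthy controls. The non-target share of 54% (46.5% with all 215 PDAC) is arithmetic from the article. The possible masking, 0.06 to 0.14 of AUC at a pooled 0.85 on the discovery mix, depends on an advanced-stage AUC of 0.90 to 0.97 and vanishes if the score performs equally at all stages. That resectable disease will be poorly detected is not demonstrated.

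**What to change.** In Aims of PANLIPSY, Statistical analysis and Endpoints, name one governing contrast. State that marker selection, tuning, the decision whether a model performs well enough, AUC and the Youden threshold are computed on resectable PDAC versus controls. Advanced cases may stay in the training data. Stratify the 60/20/20 split by stage, and report discovery AUC by stage as well, which also gives effect to the stage-based signatures announced under Discovery phase. Settle this before discovery modelling starts.

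**Cost.** Wording only, with no new patients or assays. The headline AUC will probably be lower, and each metric rests on fewer cases: a 20% share of discovery holds about 0.2 × 85 = 17 resectable patients and 17 healthy controls, giving a half-width of about 0.133 at AUC 0.85 by the same formula. Restricting training itself to the 85 resectable cases is not required; that is a separate trade-off.

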### Study population

A total of 215 patients with PDAC, 25 patients with benign pancreatic conditions (BPC) and 115 age- and sex-matched HCs will be included during the study period.

### Pancreatic ductal adenocarcinoma patients (BACAP 2 prospective clinical trial / NCT06128343)

The collection of all biological samples from patients with PDAC will be supervised by the BACAP consortium, which was developed to provide the scientific community with biological material to identify new markers, including diagnostic and prognostic biomarkers [11].

### Inclusion criteria

Age 18 years or older.Patients with cytologically and/or histologically confirmed pancreatic ductal adenocarcinoma, regardless of the cancer stage (resectable, borderline or locally advanced or metastatic).

### Exclusion criteria

Patients who have already initiated treatment for pancreatic cancerOther cancers (excluding prior pancreatic cancer or skin cancer other than melanoma) within 5 years from eligibility screening.Pregnant or nursing woman, or women of childbearing age not willing to use contraceptionProtected and vulnerable adultsIndividuals not covered by health insurancePatients unable to understand and sign written informed consent.

### Pancreatic benign lesions (PACTOL prospective clinical trial / NCT05824403)

PACTOL is a prospective cohort dedicated to pancreatic pathologies other than cancer. Its aim is to develop tools for positive or differential diagnosis between potentially malignant and benign pancreatic pathologies.

### Inclusion criteria:

Age 18 years or olderPatients with inflammatory or cystic exocrine pancreatic pathology.

